## Abstract

**Background:**

For the nearly 75% of patients living with type 2 diabetes (T2DM) that do not use insulin, decisions regarding self-monitoring of blood glucose (SMBG) can be especially problematic. While in theory SMBG holds great promise for sparking favorable behavior change, it is a resource intensive activity without firmly established patient benefits. This study describes our study protocol to assess the impact of three different SMBG testing approaches on patient-centered outcomes in patients with non-insulin treated T2DM within a community-based, clinic setting.

**Methods/Design:**

Using stakeholder engagement approach, we developed and implemented a pragmatic trial of patient with non-insulin treated T2DM patients from five primary care practices randomized to one of three SMBG regimens: 1) no testing; 2) once daily testing with standard feedback consisting of glucose values being immediately reported to the patient through the glucose meter; and 3) once daily testing with enhanced patient feedback consisting of glucose values being immediately reported to the patient PLUS automated, tailored feedback messaging delivered to the patient through the glucose meter following each testing. Main outcomes assessed at 52 weeks include quality of life and glycemic control.

**Discussion:**

This pragmatic trial seeks to better understand the value of SMBG in non-insulin treated patients with T2DM. This paper outlines the protocol used to implement this study in fifteen community-based primary care practices and highlights the impact of stakeholder involvement from the earliest stages of project conception and implementation. Plans for stakeholder involvement for result dissemination are also discussed.

**Trial registration:**

ClinicalTrials.gov NCT02033499, January 9, 2014.

## Background

Over the past decade the value of routine daily self-monitoring of blood glucose (SMBG) in patients with type 2 diabetes (T2DM) not treated with insulin has been contentiously debated [1–8]. Proponents postulate that testing promotes better awareness of glucose levels, leading to improvements in diet and lifestyle. When test results are shared with health care providers, it is argued, there is also the potential for more timely treatment modification. Competing arguments point to the costs of SMBG, both in terms of supplies (test strips and meters) and time, as well as discomfort and potentially quality of life. As a result no clear consensus exists regarding SMBG monitoring in non-insulin treated patients with T2DM.

In an attempt to make SMBG more convenient and patient-centric, much effort has been placed in improving SMBG technology [9]. Early studies that marry technology and SMBG been mixed, with some showing a benefit on glycemic control and others showing no benefit [1, 10]. Few trials have pragmatically assessed the utility of SMBG monitoring in real-life settings, like the busy primary care practice where the majority of non-insulin treated patients with T2DM are managed. With patients taking a more directive role in their health care, a large focus is being placed on how usable these glucose-monitoring tools are in the real world. Few studies have focused on the health care provider side of this issue. In fact, studies of ‘enhanced’ SMBG, where both the patient and the provider were engaged in SMBG interpretation, found A1c reductions along the magnitude of 0.5% [4, 11–13]. As additional ‘enhanced’ intervention SMBG studies have been added to the literature [13, 14], more recent reviews and meta-analyses have drawn conclusions more in favor or testing [4, 15]. This pattern suggests that, for SMBG to be an effective self-management tool in non-insulin treated T2DM, the patient and the health care provider must both actively engage in performing, interpreting, and acting upon the SMBG values.

Given these unanswered questions regarding the impact of SMBG on patient quality of life and other patient reported outcomes, there is a growing interest by patients and other stakeholders who are looking for data that will help them make better, informed decisions about their self-care when no standard of care exists and providers make recommendations based upon their experience and preferences, like SMBG monitoring in T2DM. Our overarching goal is to answer the following questions: Is SMBG testing effective for people with non-insulin treated T2DM in terms of either A1c or quality of life (QOL)? We will also examine outcomes from SMBG in patients with different baseline characteristics. Our primary outcomes include change in glycemic control over 52 weeks and change in QOL over 52 weeks. The purpose of this paper is to describe our study methods and the unique aspects of stakeholder engagement that have been employed during the design and implementation of the study.

## Methods/Design

### Study overview

The overarching goal of this proposal is to assess the impact of three different SMBG testing approaches on patient-centered outcomes in patients with non-insulin treated T2DM within the real-world, clinic setting. In this pragmatic trial, 450 patients will be randomized to one of the following three SMBG testing regimens: 1) no SMBG testing, 2) once daily SMBG testing with standard patient feedback consisting of glucose values being immediately reported to the patient through the glucose meter, and 3) once daily SMBG testing with enhanced patient feedback consisting of glucose values being immediately reported to the patient PLUS automated, tailored feedback messaging following each SMBG testing event delivered to the patient through the glucose meter.

### Recruitment

We will recruit 450 patients from primary care practices within the central North Carolina area. Patients will be randomized to one of the three study arms: 1) no SMBG testing; 2) once daily SMBG testing with standard patient feedback which includes the current glucose value; and 3) once daily SMBG testing with enhanced patient feedback which includes the current glucose value and a personalized message about the current glucose value. We have elected to use an FDA approved, cellularly-enabled glucometer device given its capabilities to deliver messaging to patients in real time. Participants in both the standard feedback and enhanced feedback groups will all receive the glucometer. Patients will be followed for 1 year. The first two study groups represent SMBG testing approaches commonly utilized in clinical practice, while the third incorporates cutting edge glucose monitoring tools now on the market. During routine clinic visits, health care providers will be guided to modify therapies based upon American Diabetes Association (ADA) guidelines, which focus on A1c values and SMBG values if available. Patients in groups 2 and 3 will also receive training in obtaining and interpreting SMBG values. SMBG values will be systematically evaluated at routine clinic visits.

### Stakeholder Engagement

As part of this grant, stakeholders were encouraged to play a role in providing perspective to the research questions and methodologies chosen, and patient related outcomes. There were several stakeholders that provided a critical role in providing care advocacy and education for persons with diabetes in North Carolina, which included patient groups community members at risk individuals policy makers providers industry and professional organizations. Given all of these stakeholder groups involved in the area of diabetes we chose a broad yet appropriately sized swath of this community. This included the North Carolina Diabetes Advisory Council, a patient advisory board, a community advisory board, health care providers, American diabetes Association representative, National Diabetes Education Program representation, as well as patients involved in the Diabetes registry and Glucometer manufacturers. Two primary methods were planned for continuing collaboration with these stakeholder groups. This included attending regularly scheduled meetings the larger organizations on a pre-stipulated basis and holding key stakeholder teleconferences with a small group (~10) of representative stakeholders.

### Patient identification and recruitment

A multi-pronged approach will be utilized to identify study participants. First, patients who have non-insulin treated T2DM will be identified using the Carolina Data Warehouse (CDW) or by chart review in the participating practice. Patients will receive an invitation letter by mail, signed by their health care provider describing the study. Any patient not interested in participating will be able to opt out of further contact by returning a post card or calling a toll-free number. If no opt out call is made within 1 week of sending the letter, telephone contact will be attempted on up to three different occasions at three different times of day. Second, we will place recruitment flyers within the participating practices that will be visible in waiting areas and exam rooms. Clinic staff will be encouraged to discuss the study with potentially eligible patients during routine clinic activities (i.e. while collecting vital signs and during check-in or check-out). The UNC field coordinators will communicate regularly with practice staff regularly regarding potentially eligible

All potentially eligible patients will be screened for eligibility by phone call. Overall inclusion and exclusion criteria are listed in Table 1. The call will take about 15 min, during which a member of the study team describes the study, answer questions, and conducts a short set of simple screening questions. Eligible interested patients complete an assessment visit with a research coordinator. To decrease patient burden and further engage participating practices, assessment visits occur at the patient’s primary care office. Assessments are separate from their appointment with their primary care provider, and may or may not occur on the same day as a regularly scheduled clinic visit, though for patient convenience we make every effort to coordinate the assessments with a regular clinic visits. During these assessments, the research coordinator reviews the study details in greater depth, verify all inclusion and exclusion criteria, and obtain written informed consent.

**Table 1 Tab1:** Monitor trial inclusion and exclusion criteria

Inclusion Criteria	Exclusion Criteria
T2DM diagnosis Age ≥ 30	Sees an endocrinologist or other diabetes specialist
An established patient at the participating practice	Use of insulin.
≥ 6.5% but ≤ 9.5%	Pregnancy
Willing to comply with random assignment into a study group	Plans to relocate in the next 12 months.
No history of significant issues with hypoglycemia	Has other conditions (e.g. renal or cardiovascular disease), factors (e.g. frailty) or comorbidities (e.g. cancer) that might put the patient at risk

### Data collection

#### Baseline

Eligible patients interested in enrolling for the study are subsequently scheduled for the initial visit with the study Field Coordinator. During this initial visit, the Field Coordinator reviews and obtains written informed consent from the patient. A signed copy is provided to the participant. After written informed consent has been received, blood samples are obtained along with height and weight. Standardized surveys are completed, and patients have the option of completing them independently or with the assistance of the Field Coordinator.

#### Randomization

After providing informed consent, baseline A1c, and completing the baseline study interview, participants will be randomized to one of the three treatment arms using sequentially numbered, opaque, sealed envelopes. The allocation sequence is generated using computer-generated randomly permuted blocks of random sizes. The randomization is stratified by study practice. The Field Coordinator reviews the treatment assignment with the patient, using a standardized script, provide the initial training and supplies necessary for participation in the study and answer any remaining questions (Fig. 1).

**Fig. 1 Fig1:**
[figure not shown]
Study Arms

#### 52 week follow-up

Patient will have blood drawn for a A1c. Patient participants will complete a follow-up interview that includes demographic, health history, and quality of life questions. Weight measurement will be collected.

#### Measures

The two primary outcomes of the study are change in A1c and change in health related quality of life (HRQOL). The A1c was chosen due to its use in prior studies and its standing as a measure on which: 1) providers evaluate patients; 2) payers evaluate providers; and 3) patients evaluate themselves and their providers [2]. Though HRQOL is also critically important to patients, few studies have rigorously examined the impact of SMBG on HRQOL. Based on these facts and the recommendations of our stakeholder groups, HRQOL is a co-primary outcome for this pragmatic trial. We will utilize the Short Form 36 (SF-36) to assess overall quality of life. We will use the physical component score (PCS) and the mental component score (MCS), with scores standardized to a normal distribution (mean = 50 and standard deviation[SD] = 10) [16]. It has been widely used and validated in medical studies generally and diabetes studies in particular [17–20]. All primary and secondary outcomes are outlined in Table 2. Because the 52-week time point may not align with a scheduled primary care visit, we have defined this time point as 52 ± 6 weeks from the baseline visit.

**Table 2 Tab2:** Primary and secondary patient-centered outcomes

	Clinical Outcomes	Time	Patient Reported Outcomes	Time
Primary	Glycemic control (A1c)	Baseline/52 weeks	Quality of life (QOL)	Baseline/52 weeks
Secondary	Hypoglycemia frequency	Baseline/52 weeks	DM-related QOL	Baseline/52 weeks
	Health care utilization	Baseline/52 weeks	DM self-care	Baseline/52 weeks
	Treatment regimen modification	Baseline/52 weeks	DM treatment satisfaction	Baseline/52 weeks
			DM-related self-efficacy	Baseline/52 weeks
			Patient-provider communication	Baseline/52 weeks

The following secondary endpoints will be collected from patient participants at baseline and 52-weeks. 1) Problem Areas in Diabetes (PAID) to assess psychological and social stress associated with diabetes [21–23], 2) Diabetes Symptom Checklist (DSC) to measure of diabetes-related symptom frequency and perceived severity during the prior month covering six symptom categories: hyperglycemic, hypoglycemic, cardiac, neuropathic, psychological, and vision-related [24–26] 3) Summary of Diabetes Self Care Activities (SDCA) survey to measure self-management activities (diet, exercise, blood glucose testing, foot-care, and smoking status and a supplemental medication adherence question [27], 4) the Diabetes Treatment Satisfaction Questionnaire (DTSQs) standard version to assess this diabetes treatment satisfaction [28], 5) Diabetes-Specific Self-Efficacy using the Diabetes Empowerment Scale Short Form [29], 6) Patient-Provider Communication using the Communication Assessment Tool [30].

#### Hypoglycemia Frequency

At the 52-week follow-up visit, participants are asked to report the number of hypoglycemic episodes that required intervention by a caregiver or by medical or paramedical personnel since enrolling in the study. For each episode, the participant will be asked whether EMS was called or led to an urgent care clinic or emergency department visit, or hospitalization. Each report is reviewed by the study principal investigators and co-investigator to determine whether the event is study related. A summary report is submitted to the UNC Institutional Review Board.

#### Health Care Utilization

Utilization outcomes will include inpatient, outpatient and emergency department utilization during the 52-week study period. UNC visits will be collected through the EHR while non UNC visits will be captured at the 52 week study visit via patient interview with the study coordinator.

#### Adverse Events

Any reported adverse events will be categorized as related or not related to the study intervention by the investigators. These events will be reported in real time to the principal investigators for confirmation and review. Regardless of causality, all unanticipated Serious Adverse Events will be reported to the IRB for review.

#### Qualitative Assessment

To gain a deeper understanding of patients’ and health care providers’ experiences with each of the SMBG testing approaches, including facilitators and barriers to dissemination, we will conduct focus group discussions at the UNCPN practices.

##### Qualitative Assessment of Patient Outcomes

Individual phone interviews will be conducted by researchers skilled in qualitative data collection. At each participating practice, we will interview approximately 6 patients who have completed the study. Two patient participants from each arm will be recruited for each of the 13 practices (*N* = 78 patients). Every effort will be made to recruit a range of high and low engagement for testing arms. Interviews will last approximately 30–45 min and will include these topics: impressions of and experience with SMBG prior to and during the trial, including using a wireless glucometer and messaging system, and impressions of using the downloaded SMBG reports at clinic visits, interactions with providers about diabetes care before and during the study, and strategies for dissemination and communication. All participants will review, sign, and be given a copy of the IRB-approved informed consent document specific to the focus groups.

##### Qualitative Assessment of Health Care Provider Outcomes

Focus groups (one per practice) with 5–10 physicians and nursing staff will also be conducted. by researchers skilled in qualitative data collection. Focus groups will be conducted once at least 80% of that practice’s enrolled study participants will have completed their 52-week follow-up visit. Key discussion topics will include: impressions regarding the usefulness of SMBG summary reports and accompanying treatment algorithm; experience with recommending SMBG for patients with NIT DM prior to and during the trial (and for both enrolled and non-enrolled patients); and perceived benefits/problems arising from being a practice site for this study. All participants will review and sign IRB-approved informed consent documents prior to participation. We will also collect age, gender, race/ethnicity, full-time/part-time employment status, years in practice, and area of practice.

## Sample Size

We desire high power for our primary between-arm comparison as well as reasonable power to detect an important effect modifier, should one exist. In a recent Cochrane Review, the estimated mean 12-month differences between SMBG and control groups were−0.13 and−0.52%, respectively, for patients diagnosed more than and less than 1 year prior to the study [1]. Assuming approximately equal enrollment of newly diagnosed and long term patients, this implies a mean difference of−0.325%. Based on results from one of the larger and better quality trials conducted to date, we assume the standard deviation for ΔA1c would be 0.8% [4]. We assume no more than 10% loss to follow-up. Given these assumptions, randomizing 150 patients per group would provide at least 90% power for the primary comparison for A1c at the 0.05 significance level. This same sample size would provide at least 80% power for the primary comparison if the true standard deviation were as high as 1.0%. For comparing mean change in HRQOL between groups, we will use the physical and mental component scores of the SF-36, both of which range from 0 to 100. Because we are interested in two different aspects of QOL, we will apply a Bonferroni correction and assess each comparison at the 0.025 level. Based on observed results from the ZODIAC-17 SMBG study, we conservatively assume that the standard deviation for the change scores for either component will be 10 points [2]. Under these assumptions, randomizing 150 patients per group with no more than 10% loss will provide at least 80% power to detect an overall difference between groups if the mean difference between the highest and lowest groups is at least 4 points.

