### Baseline Statistics

Table 3 highlights the baseline statistics of the 450 subjects that have been recruited into the study.

**Table 3 Tab3:** Baseline interview

	Mean (sd)	Min	Max	N (%)	# Missing
Demographics					
Age (years)	60.5 (11.5)	30.8	91.8		
Male				207 (46.0)	
Race					
American Indian or Alaskan Native				3 (0.7)	
Asian				9 (2.0)	
Black or African-American				148 (33.0)	
Native Hawaiian/Pacific Islander				1 (0.2)	
White				279 (62.3)	
Other (African, Filipino, Hispanic)				3 (0.7)	
Multiracial (1 = white + other, Indian)				5 (1.1)	
Refused (e.g., human race)					2
Ethnicity					
Latino/Hispanic				8 (1.8)	1
Education					
Less than high school graduate				25 (5.6)	
High school graduate or GED				107 (23.8)	
Some college or associate’s degree				164 (36.5)	
4-year college degree				92 (20.5)	
Graduate degree				61 (13.6)	
Refused					1
Marital status					
Married				292 (64.9)	
Widowed				37 (8.2)	
Living together				4 (0.9)	
Single				64 (14.2)	
Separated				7 (1.6)	
Divorced				46 (10.2)	
Comorbidities					
# comorbidities	3.4 (1.8)	0	10		
Heart disease				86 (19.2)	1
High blood pressure				340 (75.6)	
Lung disease				30 (6.7)	
Stroke				29 (6.4)	
High Cholesterol				299 (67.0)	4
Kidney disease				32 (7.1)	
Liver disease				18 (4.0)	
Anemia or other blood disease				61 (13.6)	
Cancer				76 (16.9)	
Depression/anxiety				139 (30.9)	
Arthritis				210 (46.8)	1
Chronic back pain				112 (24.9)	
Autoimmune disease				14 (3.1)	
Stomach or bowel disease				83 (18.4)	
Healthcare utilization					
Have you seen your primary care provider?	3.7 (2.4)	1	30		
Have you gone to an urgent care clinic?	0.5 (1.1)	0	12		
Have you been seen in the Emergency Room	0.4 (1.1)	0	12		
Have you been hospitalized overnight?	0.2 (0.5)	0	6		
Have you had someone call EMS for you?	0.1 (0.4)	0	5		
DM-related					
Nephropathy or other diabetes-related kidney disease				11 (2.4)	
Diabetic retinopathy or other diabetes-related eye disease				20 (4.4)	
Neuropathy or other diabetes-related nerve damage				65 (14.4)	
Years with T2DM diagnosis	8.2 (7.6)	0.1	50.0		
# Testing = Yes				338 (75.1)	
If yes, how often: at least daily				129 (38.2)	
If yes, how often: not daily, but > 1X/week				117 (34.6)	
If yes, how often: a few times a month				50 (14.8)	
If yes, how often: once a month				21 (6.2)	
If yes, how often: less than once a month				21 (6.2)	
If yes, how often told: at least daily				187 (55.5)	
If yes, how often told: not daily, but > 1X/week				53 (15.7)	

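### The A1c planning difference of -0.325% and the power claimed from it assume half the patients were diagnosed within a year, which the trial's own baseline table makes very unlikely

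*Protocol article*

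**What the plan says.** The Sample Size section starts from a systematic review in which the 12-month "differences between SMBG and control groups were−0.13 and−0.52%, respectively, for patients diagnosed more than and less than 1 year prior to the study". It then weights the two equally, "Assuming approximately equal enrollment of newly diagnosed and long term patients", and concludes that "this implies a mean difference of−0.325" percent. For variability, "we assume the standard deviation for ΔA1c would be 0.8" percent; for attrition, "We assume no more than 10% loss to follow-up". On these inputs, "randomizing 150 patients per group would provide at least 90% power for the primary comparison for A1c" at the 0.05 level, and at least 80% if the SD were 1.0%.

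Nothing else in the article supports the equal weighting. Table 1 has no criterion on time since diagnosis, and the Randomization section stratifies by practice only. Table 3, under Baseline Statistics, describes the 450 patients already recruited. Its row "Years with T2DM diagnosis" shows mean 8.2, SD 7.6, minimum 0.1 and maximum 50.0. The article prints the planning assumption and this row without connecting them.

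**The concern.** The two effects differ fourfold, so the expected overall difference depends strongly on the mix of patients. A cohort averaging more than 8 years since diagnosis does not look like one in which half were diagnosed within the past year. If the newly diagnosed share is much smaller, the plan's own figures imply an expected A1c difference well short of -0.325%, and the stated power does not describe the trial that was enrolled.

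A1c is a co-primary outcome, and the Discussion presents the trial as filling an evidence gap. A reader of a non-significant A1c result will look to the Sample Size section to judge how informative it is. A claim of at least 90% power invites the reading that a relevant effect has been excluded.

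**Working it through.** **Inputs.** From Sample Size: effects -0.13% and -0.52%, SD 0.8% (alternative 1.0%), 150 per group, 10% loss, alpha 0.05. From the analysis section: a three-group ANCOVA that must reject before each arm is compared with no testing, and a contrast of the two SMBG arms against no testing. From Table 3: duration mean 8.2, SD 7.6. Assumed here: two-sided tests, both SMBG arms shifted equally, and no variance reduction from covariates.

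**Reproducing the plan.**
- Difference: 0.5 x (-0.13) + 0.5 x (-0.52) = -0.325.
- Analysed per group: 150 x 0.9 = 135.
- One arm against none: SE = 0.8 x √(2/135) = 0.0974; 0.325/0.0974 = 3.34; power about 91%.
- Pooled contrast: SE = 0.8 x √(1/135 + 1/270) = 0.0843; 0.325/0.0843 = 3.85; power 97%.
- Three-group F test: noncentrality = 135 x (2/3) x 0.325²/0.8² = 14.85 on 2 and 402 df; power 94%.

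The 90% claim therefore reproduces. At SD 1.0 the same three figures are 76%, 87% and 79%, so the 80% claim is met by the pooled contrast.

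**Does Table 3 fit an equal split?** Let p be the share under 1 year and m its mean duration. The others then average (8.2 - p x m)/(1 - p), and the overall SD is at least √(p(1 - p)) times the gap between the two means.
- p = 0.5, m = 0.55 (evenly spread over 0.1 to 1 year): the others average 15.85 and the SD is at least 0.5 x 15.30 = 7.65. This exceeds the reported 7.6 even if all the others had the same duration.
- p = 0.5, m = 0.7: the others average 15.7 and must have an SD of only about 1.7 years.
- Upper bound on p from mean and SD alone: 7.6²/(7.6² + 7.2²) = 57.76/109.60 = 52.7%, or about 51% once the 50.0-year patient is included. Reaching it needs nearly all new cases at 1 year and nearly everyone else at one value near 15 years.
- p = 0.4, m = 0.55: the others average 13.3 with SD 5.6. This is odd for durations but not excluded by two moments.

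**What share is plausible?** The article does not say. A gamma curve matched to Table 3 (shape (8.2/7.6)² = 1.164, scale 7.6²/8.2 = 7.04) puts 8.8% below 1 year. A Weibull gives 9.5%, an exponential matched on the mean only 11.5%, and a lognormal 1.1%. These are assumptions about shape, not data.

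**Power by share.** Expected difference = -0.13 - 0.39 x share; 135 per group.

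| Share under 1 year | Difference | F test, SD 0.8 | One arm, SD 0.8 | Contrast, SD 0.8 | F test / contrast, SD 1.0 |
|---|---|---|---|---|---|
| 0% | -0.130 | 26% | 27% | 34% | 18 / 23% |
| 9% | -0.165 | 40% | 39% | 50% | 27 / 35% |
| 20% | -0.208 | 59% | 57% | 69% | 40 / 50% |
| 30% | -0.247 | 75% | 72% | 83% | 54 / 65% |
| 40% | -0.286 | 87% | 83% | 92% | 68 / 77% |
| 50% | -0.325 | 94% | 91% | 97% | 79 / 87% |

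**Detectable difference at SD 0.8, 90% power.** Contrast 0.274%, F test 0.301%, one arm against none 0.317%. The shares that deliver these are (0.274 - 0.13)/0.39 = 37%, (0.301 - 0.13)/0.39 = 44% and (0.317 - 0.13)/0.39 = 48%.

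**The case against.** The calculation was made before enrolment and is stated as conditional on its assumptions. It reproduces. Calling it an arithmetic error would be wrong, and that part of the defence stands.

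A reader might go further and say that Table 3 proves an equal split impossible. It does not. The contradiction appears when the newly diagnosed average about 0.6 year or less; with a higher subgroup mean, a contrived distribution near 50% survives, and 40% is not excluded. Very unlikely is as far as mean and SD go.

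A reader might also infer that the trial's real power is 40 to 50%. That figure belongs to an assumed share of about 9%, taken from a fitted curve. The ANCOVA adjusts for baseline A1c and seven other variables, which could help. If they explained an assumed 25% of the variance (SD 0.69), power at a 9% share would be about 51% for the F test and 62% for the contrast. Restoring 90% there would need roughly 64% (contrast) to 73% (one arm against none) explained, and the article gives no such figure.

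The Clinical Implications section cites other effects: about 0.2% for simple SMBG and closer to 0.5% for enhanced SMBG. With those as the two arm effects, F-test power would be 99.8% and contrast power 98.5%, though the simple arm alone would have 53%. So low power does not follow from the article as a whole. But the Sample Size section does not use those effects, and the derivation it does give remains unsupported.

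Finally, one might argue that the aim of "reasonable power to detect an important effect modifier, should one exist" fails for the same reason. The documents do not support that: no modifier or target power is named. Even at an equal split, a contrast-based test of the 0.39% gap between duration groups has SE 0.8 x √(2/67.5 + 2/135) = 0.169 and only about 64% power. A smaller share would worsen this but is not its cause.

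**Conclusion.** The concern holds as an unsupported planning input. The difference of -0.325%, the 90% claim and the 80% claim at SD 1.0 all depend on about half the patients being newly diagnosed. The trial's own baseline data make that very unlikely, and nothing in the design secures it. On the plan's two effects, at any share up to 30%, all three tests fall below 90% at SD 0.8, and F-test and contrast power fall below 80% at SD 1.0. The three-group test that gates the arm comparisons needs a share near 44% to reach 90%.

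The size of the shortfall cannot be fixed from the article because the share is not reported. The range rests on 135 analysed per group, equal effects in both SMBG arms and no gain from covariates. It concerns A1c only; the SF-36 calculation does not use the split.

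**What to change.** In the Sample Size section or beside Table 3:

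1. Report the number and percentage of the 450 patients diagnosed less than 1 year before baseline. This is baseline data and needs no unblinding.
2. Recompute the expected A1c difference as -0.13 - 0.39 x share, and restate the power at SD 0.8 and 1.0, naming the test to which each figure applies.
3. State what 135 per group can detect. At SD 0.8 with 90% power this is about 0.27% for the pooled contrast and 0.32% for one arm against no testing. Say that a non-significant A1c result will be interpreted from its confidence interval, not as coming from a trial with 90% power.

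The cost is a less favourable stated power. Sample size, primary test and significance level do not change.

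### The HRQOL power of at least 80% is not guaranteed by its own inputs: with 10% loss, the overall three-group test has 76.6% power if the third group lies midway

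*Protocol article*

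**What the plan says.** The Sample Size section of the protocol article gives every input for the HRQOL calculation.

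- **Test and level:** the aim is "power to detect an overall difference between groups". Because two SF-36 components are tested, "we will apply a Bonferroni correction and assess each comparison at the 0.025 level".
- **Effect:** the power applies "if the mean difference between the highest and lowest groups is at least 4 points". The position of the third group is not given.
- **Variability:** the assumption, described as conservative, is that "the standard deviation for the change scores for either component will be 10 points".
- **Sample size and claim:** "randomizing 150 patients per group with no more than 10% loss will provide at least 80% power to detect an overall difference between groups".

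The Data Management and Statistical Analysis Plan section adds two relevant facts. Missing 52-week outcomes are ignored in the primary analysis, so patients who are lost reduce the analysed number. The analysis is an ANCOVA on the change scores with baseline covariates, but the sample-size text takes no credit for variance that those covariates might explain.

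**The concern.** The sentence makes a guarantee: power of at least 80% whenever the range of the three means is at least 4 points and loss is at most 10%. A guarantee fails if any permitted pattern of means falls short. For a fixed range, an overall test of three means has least power when the third mean lies halfway between the other two, so the claim has to be checked there.

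HRQOL is a co-primary outcome. A null HRQOL result will be read against the statement that a 4-point difference would have been found with a type II error of no more than 20%. If the stated inputs allow a larger error, the statement should say so.

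**Working it through.** **Inputs** (all from Sample Size): three equal groups, 150 randomized per group, 10% loss, SD 10, level 0.025, range 4. Evaluable per group: 150 × 0.90 = 135.

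**Method.** Power of the overall F test with 2 and 3n − 3 degrees of freedom. The noncentrality is λ = n × Σ(μᵢ − μ̄)² / SD².

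**Third mean at the midpoint (0, 2, 4).** The overall mean is 2, and the sum of squares is 4 + 0 + 4 = 8.

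**Can the stated figure be reproduced?**
- n = 150, no loss: λ = 150 × 8/100 = 12.0, power 81.6%.
- n = 135, 10% loss: λ = 135 × 8/100 = 10.8, F(2, 402), power 76.6%.

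At the midpoint, the stated minimum of 80% is met with 150 per group and missed by 80 − 76.6 = 3.4 percentage points with 135.

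**Dependence on the third mean, n = 135:**

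| Means | Sum of squares | λ | Power |
|---|---|---|---|
| 0, 2, 4 | 8.00 | 10.80 | 76.6% |
| 0, 1, 4 | 8.67 | 11.70 | 80.4% |
| 0, 0.5, 4 | 9.50 | 12.83 | 84.4% |
| 0, 0, 4 | 10.67 | 14.40 | 88.9% |

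Power is below 80% while the third mean is within about 0.9 points of the midpoint, and above 80% beyond that.

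**What would restore 80% at the midpoint?** The test needs λ of about 11.6. Changing one input at a time:
- *Number evaluable:* 11.6 × 100/8 = 145 per group. That is a loss of 5/150 = 3.3%, or, at 10% loss, 145/0.90 = 161.1, so 162 randomized per group.
- *Range, with n = 135:* for range d with the third mean midway, the sum of squares is d²/2. Then d = √(2 × 11.6 × 100/135) = 4.15 points.
- *Residual SD, with n = 135 and range 4:* SD = √(135 × 8/11.6) = 9.65. The covariates would have to explain 1 − 0.965² = about 7% of the change-score variance.

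**Other readings, n = 135.** The overall test at 0.05 with the third mean midway gives 84.3%. A pairwise t test of highest against lowest at 0.025 gives 84.8%. Both exceed 80%, but the first contradicts the stated level and the second the stated overall test.

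**A1c, for comparison** (difference 0.325, both SMBG arms at that effect, level 0.05, n = 135):

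| Test | SD 0.8 | SD 1.0 |
|---|---|---|
| Pooled SMBG vs no testing | 97.0% | 86.8% |
| Overall three-group test | 94.0% | 79.1% |
| One SMBG arm vs no testing, unadjusted | 91.4% | 75.8% |

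**The case against.** **The midpoint is not a stated assumption.** This is correct, and it limits the point. The article does not place the third group, and with the loss applied there are many positions for which 80% or more is reached. The figure of 76.6% is a minimum, not the power under every pattern the inputs allow. The objection does not rescue the sentence, which promises a minimum and names no pattern.

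**The analysis is adjusted and the SD is called conservative.** Covariates explaining about 7% of the variance would be enough, so a real deficit in the adjusted analysis may well not exist. That stands as a comment on the trial. It does not make the printed figure follow from the printed inputs, because the text assumes an SD for change scores and claims no covariate gain.

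**Two stronger readings are tempting.** A reader might infer from 81.6% at 150 per group that the loss was never taken off. The documents do not show this: a calculation with 135 per group and a third mean further from the midpoint also gives at least 80%, and the A1c claim at SD 0.8 holds with the loss applied for all three tests tabulated.

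A reader might also take the A1c sentence, "This same sample size would provide at least 80% power for the primary comparison if the true standard deviation were as high as 1.0"%, as a second error, since one arm against none gives 75.8% at 135 per group and 80.1% at 150. But the article does not tie the primary comparison to a named test. The pooled contrast is a planned analysis and gives 86.8% with the loss applied, and the overall test misses by less than 1 percentage point. That is imprecise naming, not a shown arithmetic error.

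**Conclusion.** The HRQOL statement is wrong as written, by a modest amount. Under its own inputs the guaranteed power is 76.6%, a worst-case type II error of about 23% where at most 20% is implied. This rests on four things: the overall three-group test at 0.025, an SD of 10 with no covariate reduction, the full 10% loss leaving 135 analysed per group, and reading the promised minimum as covering the least favourable third mean.

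The conclusion is confined to the guarantee. It does not say that power is 77% for every pattern, how the original figure was obtained, or that the A1c claims fail. No test, level or analysis changes. The Baseline Statistics section reports that all 450 participants have been recruited, so this is a correction of a stated figure and not a case for changing the sample size.

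**What to change.** Replace the HRQOL sentence with one of the following.

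- With 135 evaluable patients per group, the overall test of each component at 0.025 has a minimum power of about 77% (76.6%) for a 4-point range, with the third mean midway, and 80% for a range of about 4.15 points.
- Keep 80% for 4 points and state the condition that makes it true: either a third mean at least about 1 point from the midpoint, or baseline covariates explaining about 7% of the change-score variance, with the basis for that assumption.

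As a related clarification, name the test meant by the primary comparison for A1c, because at SD 1.0 with 135 per group the power is 87% for the pooled contrast, 79% for the overall test and 76% for one arm against none.

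The cost is wording, and a slightly less favourable figure or an added explicit assumption.
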